### 4.2. Secondary outcomes

Erythrocyte sedimentation rate, C-reactive protein, spinal mobility (figure-ground distance, occipital tubercle-wall distance, Schober test) will be secondary indicators, which will be tested at 0th and 8th weeks of treatment.

### 4.3. Safety outcomes

Vital signs (respiration, heart rate, body temperature, blood pressure, electrocardiogram), blood routine, urine routine, stool routine, liver function, and renal function will be safety indicators, which will be tested at 0, 4, and 8 weeks of treatment. If an adverse event occurs, the clinical investigator will record it in detail on the case report form (including symptoms, time of onset, duration, examination and results). Serious adverse reactions will be reported to the Ethics Committee of the First Affiliated Hospital of Henan University of Chinese Medicine and rescue procedures will be initiated immediately.

### 4.4. Quality control and trial monitoring

Before the trial begins, all investigators will receive specialized training to ensure the quality of the study. Training includes how to select and exclude participants, how to complete randomization, how to properly implement interventions, how to record case report forms in a standard way, how to evaluate outcomes and manage data. Clinical investigators responsible for diagnosis and treatment will be registered Chinese medicine practitioners. In order to improve the compliance of the participants, the researchers will conduct health education and fully respect the participants right to informed consent. Raw data will be recorded in a case report form, and 2 data administrators will enter the data into the spreadsheet and review the data separately. To ensure the objectivity of the data, the evaluation and statistics during the trial are blinded. The lead investigator will oversee the entire trial.

### 4.5. Statistical analysis

SPSS 28.0 software (https://www.ibm.com/spss) will be used by professionals blinded to trial grouping for statistical analysis of data. Efficacy and safety analyses will be based on the intent-to-treat principle of analysis of all randomized participants. Measurement data that conform to normal distribution are represented by mean and standard deviation (‾ *x ± s*), and measurement data that are not normally distributed are represented by median and quartile (M[Q _25_, Q _75_]). Qualitative data is expressed as a %. If the data obey the normal distribution and the variance is homogeneous, the *t* test would be used for comparison; if the data does not conform to the normal distribution or the variance is unequal, the nonparametric test should be used for comparison. A 2-tailed test will be used, and *P* < .05 indicated a statistically significant difference.

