### 2.3. Participants

After obtaining informed consent, this study will include 80 AS patients with cold-dampness obstruction type. We will post printed recruitment posters in the hospital or post recruitment information on hospital social media to recruit participants, and participants who meet the research criteria will be invited to the Rheumatology and Immunology Department of the First Affiliated Hospital of Henan University of Chinese Medicine for the research. Eligible participants will be randomized 1:1 to treatment and control groups. The treatment will last 8 weeks.

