### 2.4. Sample size

The sample size calculation was performed using PASS 15 software (https://www.ncss.com/),^[7]^ with α = 0.05 (2-tailed test). The sample size was N_1_ in the treatment group and N_2_ in the control group. According to the current clinical efficacy statistics of TCM in the treatment of AS, the effective rate of the treatment group was P_1_ = 78%, while the control group P_2_ = 43%. Using the Z test, H_0_: P_1_–P_2_ = 0. H_1_: P_1_–P_2_ = D_1_ ≠ 0, calculated using the approximate normal method, N_1_ = N_2_ = 36. Considering the loss of cases, if the loss rate is 10%, and each group increases by 4 people, the final sample size is 40 cases in the treatment group and the control group, for a total of 80 cases.

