### 3.3. Combined treatment regulations

If the subjects meet the inclusion criteria, and the patients with other diseases need to continue to use the drug in the clinical trial, or if they really need to add other drugs or treatment methods due to the needs of the disease treatment, the drugs used should be recorded in the case report form in detail. name (or treatment method), dosage, frequency of administration, time of administration, etc. The drugs and treatment methods that must be taken in combination with other diseases must be recorded in detail in the combined medication table. If disease progresses during the study, participants can withdraw from the study and use other treatments. This case will be treated as an excluded case and the patient will be asked to complete relevant examinations and assessments as far as possible.

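### Section 4.5 bases safety on all randomised patients, so anyone never dosed lowers the adverse-event rate, and Section 3.3 conflicts with it on patients who withdraw to other treatment

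*Protocol article*

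**What the plan says.** The population rule is in Section 4.5: "Efficacy and safety analyses will be based on the intent-to-treat principle of analysis of all randomized participants". It is a positive statement that covers safety by name. The article mentions no separate safety population based on exposure.

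Section 3.3 deals with patients whose disease progresses: "If disease progresses during the study, participants can withdraw from the study and use other treatments". Its next sentence classes such a patient as excluded, while asking for examinations and assessments to be completed as far as possible. The only change of treatment described is withdrawal to treatment outside the trial. No crossover between the two arms is described.

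Section 4.3 has adverse events recorded with symptoms, time of onset and duration, but does not say whether events after withdrawal count. Section 2.4 sizes the trial at 36 per arm and then adds for losses: "if the loss rate is 10%, and each group increases by 4 people". That gives 40 per arm and 80 in total.

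**The concern.** Intent-to-treat protects an efficacy comparison because it keeps the randomised groups intact, and in a superiority trial the dilution it brings usually works against the new treatment. For a safety rate the dilution works the other way. A patient who never took the drug cannot have an adverse reaction to it, but still enlarges the denominator.

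This matters here because Sections 1 and 2.1 make safety part of the trial's stated purpose. Section 2.5 says double-blinding is impossible, and the arms differ visibly (a daily decoction against capsules and tablets). Some patients could therefore decline after learning their allocation.

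The second issue is that Sections 3.3 and 4.5 cannot both be followed for a patient who withdraws on progression. Section 4.5 keeps the patient in the analysis and Section 3.3 takes the patient out. The adverse-event table depends on which one the analyst applies.

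**Working it through.** **Inputs.** From Section 2.4: response rates of 78% and 43%, two-sided α of 0.05, 36 per arm before losses, 10% loss, 40 per arm after losses. Assumed, because the article gives no figure: the adverse-event rate in dosed patients, and u, the number per arm randomised but never dosed.

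**The plan's own figure.** The article states "calculated using the approximate normal method, N_1_ = N_2_ = 36" but no power. With the unpooled normal formula and an assumed power of 90%:

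n = (1.960 + 1.282)² × (0.78×0.22 + 0.43×0.57) / 0.35² = 10.51 × 0.4167 / 0.1225 = 35.7, rounded up to 36.

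Allowing for losses, 36 / 0.90 = 40. The 36 and the 40 both reproduce on that assumption. The safety point does not depend on this calculation; it needs only the 40 and the 4.

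**Dilution.** Rate reported on all randomised = rate in dosed × (40 − u)/40.

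| u per arm | Factor | Assumed 20% reads | Assumed 40% reads |
|---|---|---|---|
| 0 | 1.000 | 20.0% | 40.0% |
| 1 | 0.975 | 19.5% | 39.0% |
| 2 | 0.950 | 19.0% | 38.0% |
| 4 | 0.900 | 18.0% | 36.0% |

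The row u = 4 treats the entire loss allowance as never dosed. It is the most that the plan's own figure can support.

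**Zero events.** The one-sided 95% upper limit is 1 − 0.05^(1/n). With n = 40 it is 7.2%; with n = 36 it is 8.0%. If 4 of 40 were never dosed, using 40 understates the limit by about 0.8 points.

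**Patients who withdraw to other treatment**, in an arm of 40:

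- *Section 4.5 applied.* A patient whose only event comes after the switch adds 1/40 = 2.5 points to the rate of the arm to which that patient was randomised. Four such patients add at most 4/40 = 10 points.
- *Section 3.3 applied.* A patient who had an event on study drug leaves both numerator and denominator. With x patients having events, the rate changes from x/40 to (x − 1)/39, a fall of (40 − x)/1560. For x = 8 the rate goes from 20.0% to 17.9%. The largest fall is at x = 1, from 2.5% to 0%.

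The two readings push the rate in opposite directions, each by up to 2.5 points per patient.

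**The case against.** The strongest reply is that dilution rests on a number the article does not give. The 10% in Section 2.4 is loss of cases, not failure to start. A patient lost after the first dose belongs in both denominators. If everyone is dosed, the two populations coincide. This stands, and it is why the effect can only be given as a range starting at zero.

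A reader might infer that the rule makes the decoction look safer. The documents do not support a direction. With assumed rates of 40% (control) and 20% (decoction), a true difference of 20 points reads 18 if 4 per arm never start (36 − 18), 16 if only controls fail to start (36 − 20), and 22 if only decoction patients do (40 − 18). Unequal refusal is plausible in an unblinded trial, but nothing in the article quantifies it, and a shortfall beyond 4 per arm would exceed its own allowance.

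A reader might also infer that events on a switched treatment are credited to the opposite arm. They are not. The only switch described is to treatment outside the trial. Under 4.5 an event stays in the patient's own randomised arm, though it may belong to neither study treatment. Under 3.3 the patient is dropped.

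It can also be said that an unseen analysis plan could add a table of dosed patients, and that the onset and treatment times needed are already recorded (Sections 3.3 and 4.3). That shows the remedy is easy. It does not remove the point, because 4.5 already names the safety population, and making dosed patients the main safety set would depart from the published text. Finally, removing every event after a switch could hide delayed effects of study treatment. That is a fair warning and it shapes the fix.

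**Conclusion.** The point holds in limited form. Safety is explicitly placed on all randomised participants, which suits it less well than a population defined by exposure. Within the plan's own loss allowance, the cost is between nothing and a one-tenth relative reduction in a rate (factor 0.90), with a shift of about 0.8 points in a zero-event upper limit. These sizes rest on assumed event rates and on an assumed number of undosed patients between 0 and 4 per arm.

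The conflict between 3.3 and 4.5 needs no assumption: one keeps patients who withdraw on progression and the other excludes them. Its effect is at most 2.5 points per such patient in an arm of 40, in either direction. The overall importance is low, but the remedy costs almost nothing.

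**What to change.** Keep intent-to-treat on all randomised participants for efficacy. In Section 4.5, replace the shared rule for safety with wording such as: *Safety analyses include all participants who took at least one dose of study treatment, grouped by the treatment received. All adverse events in these participants are included; those starting after withdrawal to other treatment are flagged and also presented separately.* Flagging rather than removing keeps possible delayed effects in view.

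Reconcile Section 3.3 with 4.5 so that patients who withdraw to other treatment stay in the safety set. This concerns only their place in the analysis, not when or how they may withdraw.

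The cost is one or two sentences and slightly smaller safety denominators if some patients are never dosed. No new data are needed, since event onset and the timing of added treatments are already to be recorded.

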## 4. Outcome measures

### 4.1. Primary outcome

Visual analogue scale, bath ankylosing spondylitis disease activity index, bath ankylosing spondylitis functional index, and TCM syndrome scores will be primary indicators, which will be tested at 0th and 8th weeks of treatment.

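### Every efficacy outcome has a week-0 value, but the stated t or nonparametric test adjusts for none; ANCOVA would be more efficient, by about 10–56% more patients than a week-8 t test if r is 0.3–0.6.

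*Protocol article*

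**What the plan says.** Section 4.1 lists four primary measures (VAS, BASDAI, BASFI and the TCM syndrome score), "which will be tested at 0th and 8th weeks of treatment". Section 4.2 gives the same two time points for ESR, CRP and the spinal mobility measures, and the Abstract agrees. Each efficacy outcome therefore has its own baseline value.

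Section 4.5 sets the method for continuous data: "If the data obey the normal distribution and the variance is homogeneous, the *t* test would be used for comparison". If normality or equal variance fails, an unnamed nonparametric test is used. The significance rule is "A 2-tailed test will be used, and *P* < .05 indicated a statistically significant difference". The section mentions no covariate, ANCOVA or regression model, and it does not state whether the quantity compared is the week-8 value or the change from week 0.

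Section 2.4 sizes the trial on a binary effective rate (78% against 43%), giving 36 per arm and 40 after a 10% loss allowance. The article states no SD, no mean difference and no baseline to week-8 correlation for any score.

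**The concern.** Symptom scores, inflammatory markers and mobility measures usually track within a patient, so the week-0 value is expected to explain part of the spread at week 8. A two-group test without a covariate either leaves that spread in the error term (week-8 values) or removes it with a fixed slope of one (change scores). ANCOVA estimates the slope from the data and, apart from one degree of freedom, is at least as precise as either.

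Precision matters here. The trial has 80 patients, and its size was not derived from any of the four scores declared primary. The baseline data are being collected anyway. Leaving the compared quantity open also means that two analyses with different power fit the same sentence.

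**Working it through.** **Inputs.** From the article: two-sided 0.05 (Sections 2.4 and 4.5), 36 evaluable and 40 randomized per arm (Section 2.4), 1:1 allocation (Section 2.5). Assumed, because the article gives neither: correlation r between week 0 and week 8, taken as 0.3–0.6 with wider values shown, and equal SD σ at both visits.

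**The article's own figure.** Section 2.4 reports "calculated using the approximate normal method, N_1_ = N_2_ = 36" without stating power. With the unpooled normal approximation and an assumed 90% power:

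n = (1.960 + 1.282)² × (0.78×0.22 + 0.43×0.57) / 0.35² = 10.507 × 0.4167 / 0.1225 = 35.7, so 36. Then 36/0.9 = 40.

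The stated size reproduces under that assumption and is not disputed. It concerns a binary rate and does not determine power for the scores.

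**Variance of the treatment difference, n per arm.**
- t test on week-8 values: 2σ²/n
- t test on changes: 2(1−r) × 2σ²/n
- ANCOVA: (1−r²) × 2σ²/n

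The efficiency of ANCOVA is therefore 1/(1−r²) relative to the week-8 test, and 2(1−r)/(1−r²) = 2/(1+r) relative to the change-score test.

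**Gain and power.** Power is from the noncentral t with 36 per arm and an illustrative difference of 0.5 SD. The noncentrality is 0.5 × √(36/2) = 2.12 for the week-8 test (70 df). It is divided by √(2(1−r)) for changes (70 df) and by √(1−r²) for ANCOVA (69 df).

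| r | Gain over week-8 test | Gain over change test | Power, week-8 | Power, change | Power, ANCOVA |
|---|---|---|---|---|---|
| 0.1 | 1% | 82% | 55% | 34% | 56% |
| 0.3 | 10% | 54% | 55% | 42% | 59% |
| 0.5 | 33% | 33% | 55% | 55% | 68% |
| 0.6 | 56% | 25% | 55% | 65% | 74% |

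At r = 0.5 the change-score variance factor is 2(1−0.5) = 1, so the two unadjusted tests coincide and ANCOVA gains the same over both. Against the week-8 test, 36 per arm then works like 36/0.91 = 40 (r = 0.3) to 36/0.64 = 56 (r = 0.6). Above the assumed range, the gain over the week-8 test is 96% at r = 0.7.

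**Cost.** Estimating the slope reduces efficiency by the factor (2n−4)/(2n−3) = 68/69, about 1.5%. At r = 0.5 the gain falls from 33% to 31%. The noncentrality falls from 2.45 to 2.43, which takes the 68% power to about 67%.

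**Chance imbalance, week-8 reading, 40 per arm.** The standardized baseline difference has standard error √(2/40) = 0.224. It exceeds 0.3 SD with 18% chance and 0.4 SD with 7.4% chance, and lies below 0.2 SD with 63% chance. Given an imbalance of b SD and no treatment effect, the week-8 statistic is approximately normal with mean r·b/0.224 and variance 1−r². At r = 0.5 the conditional two-sided error is 2.4% at b = 0, 7.0% at b = 0.3 and 11.0% at b = 0.4. Averaged over all randomizations it is 5%.

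**The case against.** The strongest reply is that nothing here is invalid. A t test without covariates is unbiased under randomization, and this is a condensed article whose full analysis plan may say more. The first part stands and limits the point to efficiency. The second does not remove it: Section 4.5 goes beyond omitting detail and names the test, and neither reading of that test adjusts for baseline as ANCOVA does.

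A reader might infer that the plan discards the baseline data. The text does not support that. A change-score t test fits Section 4.5 equally well and does use week 0, only with a fixed slope. The defensible statement is that no baseline covariate is named and the compared quantity is unspecified.

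A reader might also infer an inflated false-positive rate from the conditional errors above. That would be wrong. The 11.0% figure applies at an imbalance of 0.4 SD, which is exceeded with 7.4% chance; it should not be paired with the 18% chance of exceeding 0.3 SD. Below 0.2 SD, the most common case, the conditional error is under 5%.

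It is also fair to object that the correlation and the 0.5 SD effect are not the article's figures, and that one range of r need not suit VAS, CRP and spinal mobility alike. This stands: the size of the gain is conditional, and at r near 0.1 the gain over a week-8 test is negligible. Nor does it show that any stated power is lost, because the sample size rests on a binary rate.

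**Conclusion.** The point holds as one of lost efficiency. The stated comparison for the continuous efficacy outcomes is valid but uses the week-0 measurements less well than it could, and it leaves open which quantity is tested. Under equal SDs and an assumed r of 0.3–0.6, the loss equals about 10–56% more patients if week-8 values are compared and 25–54% more if changes are compared. The direction does not depend on which reading is correct, apart from the one degree of freedom when r is near zero; the size depends wholly on r. This is a worthwhile improvement in an 80-patient trial, not an error that threatens its conclusions.

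**What to change.** Before unblinding, add a rule to Section 4.5 for the continuous efficacy outcomes only:

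- Compare the week-8 value between groups by ANCOVA with treatment and the baseline value of the same outcome, and report the adjusted mean difference with a 95% CI.
- Analyse CRP and ESR on the log scale, with log baseline as covariate, and report the back-transformed ratio with a 95% CI.
- Keep a rank-based analysis as a sensitivity analysis for clearly non-normal outcomes.
- Retain the existing t/nonparametric sentence for continuous safety data. Section 4.5 covers efficacy and safety together, so deleting that sentence would leave those data without a test.

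This needs no extra patients, visits or measurements, and SPSS, the software already named, fits the model. The cost is the wording and one degree of freedom, about 1.5% of efficiency at this size.

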### 2.5. Randomization and blinding

This trail will use random assignment concealment. Participants who provide informed consent and meet the inclusion criteria will be randomly assigned in a 1:1 ratio to treatment and control groups. Randomization will be based on random numbers generated by the computer. Independent researchers will prepare the distribution in an opaque envelope containing the distribution sequence number and are responsible for concealing the distribution sequence. Due to the specificity of the intervention, double-blinding was impossible. Outcome assessors, data curators will be unaware of treatment assignments.

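### Normal data with unequal variances go to a rank test while being reported as means, so the P value does not test the reported contrast; the numerical cost at 1:1 is modest

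*Protocol article*

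**What the plan says.** Protocol section 4.5 (Statistical analysis) allows the t test only when the data are both normal and homogeneous in variance. Otherwise, "if the data does not conform to the normal distribution or the variance is unequal, the nonparametric test should be used for comparison". Either failure is enough to trigger the switch. Neither the nonparametric test nor the checks that trigger it are named.

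The summary statistics in the same section depend on normality alone: mean and SD if normal, median and quartiles if not. Variance plays no part in that choice.

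The level is stated as "A 2-tailed test will be used, and *P* < .05 indicated a statistically significant difference". The rule covers all measurement data, so it applies to the four primary outcomes in section 4.1 (VAS, BASDAI, BASFI, TCM syndrome score) and to ESR, CRP and spinal mobility in section 4.2. All are measured at weeks 0 and 8. Patients are "randomly assigned in a 1:1 ratio to treatment and control groups" (section 2.5), and section 2.4 sets the size: "the final sample size is 40 cases in the treatment group and the control group, for a total of 80 cases".

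**The concern.** There are three linked problems.

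- **Wrong remedy.** The Mann-Whitney test refers its statistic to a null distribution in which the two arms are identical. It compares location only if the arms share a shape. Unequal variance breaks that condition, so it is a reason against the rank test rather than for it. The direct remedy for unequal variance in normal data is Welch's t test, which the rule bypasses.
- **Summary and test do not match.** For normal data with unequal variances the reader would see two means with SDs beside a P value that does not test their difference.
- **The data choose the method.** The test depends on features of the outcome data themselves, so the four primaries could end with different tests, settled only after the data are seen.

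At stake are the interpretation of the primary P values, some excess of false positives, and a little power.

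**Working it through.** **Inputs from the protocol.** Two-sided 5% level, 1:1 allocation, 36 per arm before loss and 40 after (sections 2.4, 2.5, 4.5). No outcome SD, variance ratio or distribution is given.

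**Inputs assumed.** The nonparametric test is Mann-Whitney. The checks are Shapiro-Wilk in each arm and mean-centred Levene, each at 0.05. SD ratios are scanned.

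**Step 1: the plan's own figure.** Section 2.4 gives "calculated using the approximate normal method, N_1_ = N_2_ = 36" for rates of 78% and 43%. The unpooled normal formula is

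n = (z₀.₉₇₅ + z₁₋β)² × [p₁(1−p₁) + p₂(1−p₂)] / (p₁−p₂)².

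Power is not stated. At 90% it gives (1.960 + 1.282)² × (0.1716 + 0.2451) / 0.35² = 10.507 × 0.4167 / 0.1225 = 35.7, so 36. Then 36 / 0.9 = 40. Both figures reproduce, with 90% power inferred. The calculation is for a binary effective rate and does not depend on the clause under review; it only supplies the arm sizes.

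**Step 2: large-sample size of the rank test, normal data, equal means, 1:1.** With SD ratio r, let c₁ = r²/(1+r²) and c₂ = 1/(1+r²). The true variance of the Mann-Whitney statistic divided by its assumed null variance is

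V = [arcsin(c₁) + arcsin(c₂)] / (2π) ÷ (1/6),

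and the actual size is 2 × [1 − Φ(1.96/√V)].

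- r = 2: c = 0.8 and 0.2; V = (0.9273 + 0.2014)/(2π) × 6 = 1.078; size 5.9%.
- r = 3: c = 0.9 and 0.1; V = (1.1198 + 0.1002)/(2π) × 6 = 1.165; size 6.9%.
- Limit, one variance going to zero: V = 0.25 × 6 = 1.5; size 10.95%.

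**Step 3: simulation at the trial's arm sizes, normal data, equal means.**

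| SD ratio | Rank test, 36/36 | Rank test, 40/40 | Whole rule, 40/40 | Welch, 40/40 |
|---|---|---|---|---|
| 1.5 | 5.3% | 5.4% | 5.0% | 4.8% |
| 2 | 5.7% | 6.2% | 5.4% | 4.9% |
| 3 | 6.8% | 6.9% | 6.6% | 4.9% |

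The rank-test columns use 40,000 runs (standard error √(0.05 × 0.95/40,000) = 0.1 point). The last two columns use 12,000 (0.2 point). At ratio 1.5 the rule and Welch are indistinguishable; at 3 they clearly differ. The ordinary pooled t test also stays at 5.0-5.3% at 40/40 for SD ratios from 1 to 10, so with equal arms the switch does not repair a failing t test.

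**Step 4: power, normal data, 36 per arm, difference 0.9, SDs 1 and 1.8.** For Welch, the standard error is √[(1 + 3.24)/36] = 0.343 and 0.9/0.343 = 2.62. With about 55 degrees of freedom the critical value is 2.00, so power is about Φ(2.62 − 2.00) = 73%. Simulation (6,000 runs) gives 72.6% for Welch and 69.9% for the rule, a loss of 2.7 points. A separate set of 12,000 runs gives 73.4% and 70.2%, a loss of 3.2.

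**Step 5: skewed data with equal means and unequal spread, 36 per arm.** These scenarios show which condition produces the large rejection rates.

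| Scenario | Rule rejects | Runs reaching rank test by variance condition alone | Medians |
|---|---|---|---|
| Gamma, mean 3, SD 1.5 v 2.25 | 10.5% | 2% | 2.75 v 2.46 |
| Gamma, mean 3, SD 1 v 2 | 15.0% | 13% | 2.89 v 2.57 |
| Lognormal, mean 10, CV 0.6 v 1.2 | 34% | 0% | 8.57 v 6.40 |

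In the gamma cases, the runs that entered by the variance condition alone were rejected about 4-5% of the time. Elsewhere, among runs passing Shapiro-Wilk and failing Levene at 40/40, the rank test rejected 6.5% (gamma shapes 16 v 4; Welch in the same runs 5.6%) and 9.3% (lognormal sigma 0.25 v 0.5; Welch 7.7%, in only 8.3% of all runs).

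**The case against.** The strongest reply is that the clause does little numerical harm here. Allocation is 1:1, inflation is one to two points at SD ratios of 2 to 3, the power loss is small, and the protocol gives no SDs from which to say that unequal spread is likely. All of that stands, and it sets the size of the point. It does not remove the mismatch: the rule still attaches a rank P value to a pair of means when a test suited to those means exists.

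A reader might infer something stronger: that switching to ranks under unequal variance pushes false positives to 10-15% or more. The documents do not support this. Those rates need skewed data. In the scenarios of step 5 some 85-100% of runs reach the rank test through non-normality, and section 4.5 summarises such data by medians, which really do differ there. Rejecting when medians differ is not plainly a false positive for a plan that never states a mean difference as its target for such data. It remains true that under unequal spread Mann-Whitney is not a strict test of medians either, but that is a separate point from the variance clause. In normal data, 10% or more at SD ratios up to 4 needs clearly unbalanced arms with the smaller arm more variable, for example 10.2% at 40/28 with SD ratio 4. Loss of 20% in the more variable arm only (40/32) gives 5.9-8.3% at ratios 1.5 to 3.

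Nor can the 34% lognormal figure be used to argue for a log-scale analysis of CRP and ESR. Welch's test on logs rejects about 35% of the time in that same scenario, because the geometric means differ (6.40/8.57 = 0.75).

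Finally, names of pre-tests, cut-offs and effect estimates with intervals may sit in a fuller protocol or analysis plan. Their absence from an article is not the criticism; the switching rule is stated outright, and that is.

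**Conclusion.** The point holds as a poorly chosen rule with a modest numerical effect. For normal data with unequal variances, section 4.5 reports means but tests ranks, and lets the observed data make that choice outcome by outcome. At 36 to 40 per arm and 1:1, the false-positive rate is about 5-7% for SD ratios up to 3 against about 5% for Welch, and the large-sample ceiling is near 11%. Power falls by about 3 points in the scenario examined.

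These sizes rest on assumed SD ratios, on Mann-Whitney as the unnamed test, on Shapiro-Wilk and Levene as the checks, and on arms staying close to equal. The mismatch between summary and test rests on none of them; it follows from the wording of section 4.5. This should be corrected, but it does not by itself undermine the trial.

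**What to change.** Replace the data-driven switch in section 4.5 with one method per outcome, named before the data are seen.

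- **VAS, BASDAI, BASFI, TCM syndrome score and spinal mobility:** a mean-based comparison at week 8, either Welch's t test or, preferably, ANCOVA adjusting for the week 0 value with heteroscedasticity-robust standard errors. Report the difference in means from the same model, so that estimate and P value agree.
- **Rank test:** keep it as a named sensitivity analysis.
- **CRP and ESR:** if they are analysed on the log scale, state that the target is a ratio of geometric means. That is a choice of target and needs its own justification.

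The cost is wording only. The week 0 values are already collected under sections 4.1 and 4.2, and neither the sample size nor the visit schedule changes. Because the change replaces a published rule, date it and make it before the outcome data are examined.
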